#### 2.2.1. Participants

A total of 40 healthy participants, aged 18 to 50 years, will be recruited for a randomized-controlled study and categorized based on their attitudes toward COVID-19 vaccination:Vaccine-Hesitant/Resistant Group (*n* = 20): Individuals reluctant to receive the COVID-19 vaccine, identified using validated psychometric tools, including the Vaccine Hesitancy Scale [26] and the Vaccine Hesitancy Scale for COVID-19 Vaccination [27].Vaccine-Accepting Group (*n* = 20): Individuals who are vaccinated or express no hesitation toward vaccination. They will serve as controls.

Recruitment will be conducted through online advertisements and university mailing lists. To ensure comparability, groups will be matched by demographic variables, including age, gender, and educational level.

#### 2.2.2. Sample Size Calculation

The sample size was determined a priori through power analysis using GPower 3.1 [28], targeting the primary statistical test: a mixed-model ANOVA with 2 between-subjects groups (Vax vs. No-Vax), and 2 within-subjects factors—stimulus (CS+ threat-associated stimulus vs. CS− safety-associated stimulus) and time (3 SCR measurements: habituation, acquisition, extinction recall). The analysis aimed to detect a medium effect size (f = 0.25), with 95% power at an alpha level of 0.05. A moderate correlation of r = 0.5 was assumed among the six repeated measurements (2 stimuli × 3 phases), based on prior psychophysiological research and expected consistency in responses influenced by individual differences in disgust sensitivity and anxiety. This correlation was explicitly specified in GPower to ensure accurate estimation. Under the assumption of ideal sphericity (ε = 1), a minimum of 40 participants is required.

### 2.3. Inclusion Criteria

Age range of 18–50 years.Right-handedness, evaluated by the Edinburgh Inventory [30].Normal vision.

### 2.4. Exclusion Criteria

History of neurological or psychiatric disorders.Central nervous system-acting medications.Contraindications for Transcranial Magnetic Stimulation (TMS) [31].History of substance abuse or alcohol dependence.Participation in other neurophysiological studies within the last six months to avoid potential carryover effects.

### 2.5. Screening and Psychological Assessments

Participants will first complete an online screening questionnaire to verify eligibility. Eligible individuals will attend an in-person laboratory session, where written informed consent will be obtained prior to assessments.

Each participant will undergo a comprehensive psychological evaluation using validated instruments designed to assess emotional, cognitive, and ideological dimensions.Disgust Sensitivity Scale [32]: Evaluates individual sensitivity to disgust. Individuals with high disgust sensitivity may react more strongly to perceived bodily invasions (e.g., needles, foreign substances), associating vaccines with contamination or violation of purity. This heightened aversive response can contribute to intuitive vaccine rejection rooted in pathogen avoidance and moral purity schemas.State-Trait Anxiety Inventory [33]: Assesses both situational (state) and dispositional (trait) anxiety levels. Elevated trait anxiety may increase health-related fears, including vaccine side effects, leading to avoidant behaviors. High state anxiety during periods of public health uncertainty (e.g., pandemics) may amplify mistrust in medical systems or increase susceptibility to fear-based misinformation.Revised Green et al. Paranoid Thoughts Scale [34]: Measures paranoia-related cognitive patterns. Higher levels of paranoia are associated with suspicion toward authorities, including health institutions and pharmaceutical companies. Individuals with elevated paranoid thinking may interpret public health messages as manipulative or coercive, fostering conspiratorial beliefs about vaccines.Interpersonal Reactivity Index [35]: Assesses empathy through Empathic Concern and Personal Distress subscales. High empathic concern might reduce hesitancy, as empathy fosters prosocial motivation, including protecting vulnerable populations through herd immunity.Updated Rokeach Dogmatism Scale [36]: Evaluates the degree of rigid, dogmatic thinking. High dogmatism reflects cognitive rigidity and resistance to information that contradicts pre-existing beliefs. Dogmatic individuals are less likely to accept evolving scientific recommendations and more prone to ideologically driven vaccine skepticism, especially if their belief system is anti-establishment or mistrustful of science.Political Orientation: Determines self-reported political inclination (liberal, centrist, or conservative) through a direct verbal question during the screening process. Moreover, we will include left-right self-placement [37]. Compared to liberal, Conservatives may show higher hesitancy in contexts where vaccines are framed as government mandates.

### 2.6. Techniques

#### 2.6.1. Experiment 1

##### Transcranial Magnetic Stimulation (TMS) and Motor Evoked Potentials (MEPs)

To determine the optimal scalp positions (OSP) for stimulation, transcranial magnetic stimulation (TMS) will be applied using a 70 mm figure-of-eight coil connected to a MagStim Super-Rapid stimulator (The Magstim Company, Wales, UK) placed over the left M1. MEPs will be recorded via a Biopac MP-36 (BIOPAC Systems, Inc., Goleta, CA, USA) electromyographic system. Ag-AgCl Self-adhesive surface electrodes (15 × 20 mm diameter) will be placed over the right deltoid (target muscle, reference over the acromion process) and the right extensor carpi radialis (ECR; control muscle, reference over the dorsal wrist). We will place the ground electrode over the right elbow. The ECR was selected as the control muscle because, like the deltoid, it is located in the upper limb, allowing for topographically matched comparisons within the same somatomotor cortical region. In the context of MEPs elicited via TMS, this is critical: upper limb muscles are represented adjacently in the lateral primary motor cortex, allowing for consistent stimulation parameters (e.g., coil orientation, hotspot location) and minimizing anatomical confounds.

The coil will be held tangentially to the scalp, with the handle oriented at approximately 45° posterolaterally to the midline, in accordance with standard procedures for optimal activation of the primary motor cortex [38,39].

The coil will be systematically shifted in 1 cm increments over the motor cortex to identify the OSP for each muscle, which will be marked on the scalp using a makeup pencil. Once the OSP is determined, the resting motor threshold (rMT) will be established, defined as the lowest stimulation intensity capable of eliciting at least five MEPs of ≥50 μV in amplitude across ten consecutive magnetic pulses. EMG signal will be continuously recorded throughout the experimental session to confirm the absence of muscular pre-activation. It will be band filtered (5 Hz–2.5 kHz, sampling rate 10 kHz), digitalized, and stored for offline analysis. To ensure comparability across participants, all MEP amplitudes will be log-transformed (log value in mV + 1) to reduce skewness. Mean MEP amplitudes for each condition will be then normalized and expressed as a % of the baseline.

MEP peak-to-peak amplitudes (in mV) will be stored for offline analysis. The inter-stimulus interval was set at 8500 ms. In this way, the TMS frequency during experimental blocks was < 0.1 Hz to avoid that TMS per se would influence M1 excitability [40]. See Figure 1 for a diagram of the typical experimental session.

The magnetic stimulation will be delivered at random times ranging between 1100 and 1400 ms from onset of the picture to avoid any priming effects that might influence MEP amplitude like in previous studies of our group [41,42,43].

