### 2.7. Interventions

#### 2.7.1. Experiment 1

Prior to the experimental session, participants will complete demographic and psychological questionnaires. Following screening, the optimal scalp positions (OSP) and resting motor threshold (rMT) for the target (deltoid) and control (extensor carpi radialis) muscles will be determined. Participants will be seated 80 cm from a computer screen in a dimly lit room. The experimental visual stimuli will consist of pictures depicting scenes of vials and ongoing injections referring to blood sampling, COVID-19 vaccine, and influenza vaccine subtending a 10.5 × 5.8 cm region plus a neutral control stimulus consisting of a scrambled picture of the same dimension and form (see Figure 2).

For each type of stimulus in both blocks, 20 MEPs will be recorded. To ensure a balanced and unbiased presentation, stimuli will be randomly presented. A total of 16 MEPs per muscle and condition will be obtained and stored for offline analysis.

During stimulus presentation, TMS pulses will be delivered at 120% of rMT at randomized intervals (1100–1400 ms post-stimulus onset) to mitigate priming effects. EMG will record muscle activity from the levator labii superioris, which is associated with disgust responses, and the corrugator supercilii, linked to fear responses. Additionally, following the TMS session, participants will be presented again with the same set of pictures and will ask to rate their emotional responses using a 7-point Likert scale, where 1 indicated no emotional reaction and 7 indicated a very strong emotional reaction. Specifically, they were asked to evaluate the extent to which each image elicited feelings of alarm, disgust, fear, and anger.

#### 2.7.2. Experiment 2

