### 2.8. Statistical Methods

All statistical analyses will be conducted using Jamovi (version 2.6.23), an open-source statistical software based on the R 4.5.0 framework. A significant threshold of *p* < 0.05 will be applied to all analyses. Parametric methods will be employed under the assumptions of normality and homogeneity of variance, verified by Shapiro-Wilk or Kolmogorov-Smirnov and Levene’s tests, respectively. Non-parametric tests will be used if assumptions are violated.

#### 2.8.1. Experiment 1

A 2 × 2 × 3 mixed-design ANOVA will be conducted to analyze differences in MEP amplitudes, with group (Vax vs. No-Vax) as a between-subjects factor, muscle (deltoid vs. extensor carpi radialis), condition (Blood, COVID-19, influenza), as within-subjects factors.

EMG activity from the levator labii superioris (disgust) and corrugator supercilii (fear) will be analyzed using a 2 × 2 × 3 mixed-design ANOVA, incorporating group (Vax vs. No-Vax), muscles (levator labii superioris, corrugator supercilii), condition (Blood, COVID-19, influenza).

Significant interactions (*p* < 0.05) will be followed by Tukey’s HSD post hoc tests to identify condition-specific effects.

#### 2.8.2. Experiment 2

Habituation, fear acquisition, extinction, and recall will be assessed through Skin Conductance Response (SCR) amplitudes using a 2 × 2 × 3 mixed-design ANOVA. The analysis will compare responses to stimuli (CS+ threat-associated stimulus, CS− safety-associated stimulus) as a within-subjects factor, across groups (Vax vs. No-Vax) as a between-subjects factor and phases (habituation, fear acquisition, fear extinction) as a within-subjects factor. Similarly, subjective fear/disgust ratings (Likert scale) will be analyzed using a 2 × 2 × 3 mixed-design ANOVA, with group (Vax vs. No-Vax) as a between-subjects factor, and stimulus Type (CS+ vs. CS−) and phase (habituation, fear acquisition, fear extinction) as within-subjects factors. Significant interactions (*p* < 0.05) will be followed by Tukey’s HSD post hoc tests to identify condition-specific effects.

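### Dividing log(mV + 1) values by a baseline makes the MEP outcome depend on MEP size and unit, and can create a false muscle × condition effect

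*Protocol article*

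**What the plan says.** The outcome is defined in the TMS and MEP part of section 2.6.1, in two ordered steps. First, "all MEP amplitudes will be log-transformed (log value in mV + 1) to reduce skewness", with the purpose given as "To ensure comparability across participants". Second, "Mean MEP amplitudes for each condition will be then normalized and expressed as a % of the baseline". The unit is fixed in the same section: "MEP peak-to-peak amplitudes (in mV) will be stored for offline analysis".

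This outcome feeds section 2.8.1: "A 2 × 2 × 3 mixed-design ANOVA will be conducted to analyze differences in MEP amplitudes", with group, muscle (deltoid, ECR) and condition (blood, COVID-19, influenza) as factors. Section 2.7.1 adds that "A total of 16 MEPs per muscle and condition will be obtained and stored for offline analysis" and that "TMS pulses will be delivered at 120% of rMT". It also lists the pictures, "plus a neutral control stimulus consisting of a scrambled picture of the same dimension and form", but does not call the scrambled picture a baseline. Section 2.6.1 makes ECR the control muscle, and section 3.1 predicts lower deltoid MEPs in hesitant participants viewing COVID-19 vaccination.

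**The concern.** On a log scale a proportional change is a difference. Dividing one log by another does not recover it, and the + 1 ties the result to the millivolt. For small MEPs log(1 + x) is close to x, so the ratio stays near the true one. For large MEPs it is pulled towards 100%. Two muscles, or two people, with the same proportional change then get different scores only because their MEPs differ in size.

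This matters because muscle is a factor in the primary analysis, and the contrast of deltoid with ECR carries the claim that any effect is specific to the vaccinated muscle. Stimulating at a fixed percentage of resting threshold does not make MEPs equally large in the two muscles, and nothing else in the article does so.

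**Working it through.** The plan states no figure to reproduce. The check is on the formula, followed by simulation under stated assumptions.

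**1. The formula.** For baseline amplitude *b* (mV) and true ratio *c*, the planned score at a single amplitude is 100 × ln(1 + *cb*) / ln(1 + *b*). The base of the logarithm cancels.

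True 30% fall (*c* = 0.7):
- *b* = 0.1: ln 1.07 / ln 1.10 = 0.0677 / 0.0953 → 71.0%
- *b* = 1: ln 1.7 / ln 2 = 0.5306 / 0.6931 → 76.6%
- *b* = 2: ln 2.4 / ln 3 = 0.8755 / 1.0986 → 79.7%

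True 20% fall (*c* = 0.8): 81.4% at 0.2 mV, 84.8% at 1 mV, 87.0% at 2 mV, 89.8% at 5 mV. A true 50% rise reads 143.9% at 0.2 mV and 126.2% at 2 mV.

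**2. Dependence on the unit.** A 30% fall from 1 mV reads 76.6% in millivolts. In microvolts it would be ln 701 / ln 1001 = 6.5525 / 6.9088 → 94.8%.

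**3. What this does to the muscle contrast.** Take 0.3 mV in deltoid and 1.2 mV in ECR (assumed) and the same 30% fall in both. Deltoid reads ln 1.21 / ln 1.3 = 0.1906 / 0.2624 → 72.7%. ECR reads ln 1.84 / ln 2.2 = 0.6098 / 0.7885 → 77.3%. The gap of about 4.7 points is purely an artefact. If it appears in some conditions and not in others, it is a muscle × condition interaction.

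**4. Simulated error rates.** From the plan: 40 participants, 20 per group, 16 trials per muscle and condition, the 2 × 2 × 3 ANOVA, α = 0.05. Assumed: lognormal MEPs, log-SD 0.6 between persons and 0.5 between trials, baselines 0.3 / 1.2 mV. Runs of 1000 to 2000 replicates; the Monte Carlo standard error near 5% is about 0.7 points with 1000.

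| Scenario (same true change in both muscles) | Term | False rate, planned score |
|---|---|---|
| 30% fall in one condition | muscle × condition | 34.5–39% across separate runs |
| 30% fall in two conditions | muscle × condition | 39.7% |
| As the first row, plus person × muscle × condition log-SD 0.10 / 0.20 | muscle × condition | 23.6% / 15.5% |
| 20% fall in one condition, plus SD 0.10 | muscle × condition | 14.7% |
| 30% fall in one condition, baselines 0.2 / 0.4 mV | muscle × condition | 6.2% |
| 30% fall in all three conditions | muscle × condition | 3.8% |
| No true change | muscle × condition | 5.4% |
| 30% fall in one condition, hesitant group only | group × muscle × condition | 10–11% |
| 30% fall in one condition, both groups | group × muscle × condition | 5–6% |

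Further runs with person × muscle × condition variance gave 12–27% for muscle × condition.

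**5. A second set of assumptions.** Log-SD 0.5 between persons, 0.6 between trials, 0.10 for person × muscle × condition, and a fall in the COVID-19 condition only. For 0.3/1.0, 0.3/2.0 and 0.2/1.5 mV the false muscle × condition rates are 10.2%, 21.1% and 19.9% with a 20% fall, and 22.0%, 62.8% and 53.8% with a 40% fall. With equal muscles (0.3/0.3 mV) they are 5.1% and 4.8%. If the fall occurs in hesitant participants only, the three-way rate with unequal muscles is 6.3–8.9% (20% fall) and 8.6–18.0% (40% fall).

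**6. Alternatives under the same second set.** With a change common to both muscles or with none, the false muscle × condition rate is 4.3–6.0% for % of baseline on raw mV and 4.4–5.7% for a difference of mean logs.

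**The case against.** A reader might infer that the planned score creates false interactions in any event, or that the error rate is simply 40%. Neither follows. Inflation needs two things together: muscles with different MEP sizes, and a real change shared by both muscles that differs between conditions. Take away either and the rate returns to about 5%. The 40% is the top of a range; it falls with a smaller effect, with amplitudes closer together, or once people vary in how each muscle responds. Every amplitude and SD behind these rates is assumed, and the four-fold muscle difference is a choice. This objection stands and limits the claim.

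A reader might also infer a false difference between groups. That would require groups with different baseline MEP sizes, which the article gives no reason to expect.

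The hypothesis in section 3.1 is closest to the three-way term, where inflation is modest and arises only if the non-specific fall is confined to, or larger in, one group. That also stands. Muscle × condition is nonetheless tested in the same ANOVA, and its significant interactions lead to post hoc tests.

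A different reading of the text does not help. If the log step means log(mV) + 1, a 20% fall at 0.2 mV with natural logs reads (ln 0.16 + 1) / (ln 0.2 + 1) = (−0.8326) / (−0.6094) → 136.6%, a fall shown as a rise. If the percentage was meant on raw means, the text should say so, because it logs all amplitudes and only then normalises.

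Finally, a log difference without the + 1 is not immune to recording noise. With a half-normal noise term of SD 0.03–0.05 mV added to each trial (assumed), its false rate was 10–14% at 0.3 / 1.2 mV and 69% at 0.1 / 1.2 mV. It is therefore not the only valid remedy, nor a flawless one.

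**Conclusion.** The concern holds in a limited form. The distortion itself is arithmetic and needs no assumption: the same proportional change gets a different score according to MEP size and unit, contrary to the stated aim. It is a rule fixed in the article, not a detail left to another document.

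The consequence for the ANOVA is conditional. With 0.3 versus 1.2 mV and a 20–30% fall in one condition shared by both muscles, the false muscle × condition rate is about 12–40% at a nominal 5%. The group × muscle × condition rate is about 10% if a 30% fall occurs equally in both muscles of the hesitant group only. With equal muscle sizes, no true change, or the same fall in all three conditions, there is no inflation. Confidence in the mechanism is high; confidence in the size is moderate, because the documents give no amplitudes. The rule should be changed before analysis.

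**What to change.** Do not divide log(mV + 1) values. In section 2.6.1, adopt one of these and state it:

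- compute % of baseline from mean raw mV amplitudes for each muscle and condition, and log that ratio if it is skewed; or
- analyse the mean log amplitude in the condition minus the mean log amplitude at baseline, without the + 1, with a floor for near-zero MEPs fixed in advance, and back-transform to % for display only.

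Name the baseline in the same sentence. The scrambled-picture trials of section 2.7.1 are the likely candidate, but that is an inference.

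The cost is one sentence and a small code change, with no new data. The log difference gives near-threshold MEPs more weight, so its floor must be set before the data are seen; the raw percentage avoids that constant.

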##### Electromyography (EMG)

EMG signals will be recorded using a BIOPAC MP-36 system (BIOPAC Systems, Inc., Goleta, CA, USA). The signals will be amplified (×1000) and filtered with a 100–500 Hz bandpass. Electrodes will be positioned on the left side of the face, targeting the levator labii superioris (associated with disgust) and the corrugator supercilii (associated with fear), following standard placement guidelines [44]. We will remove artifacts commonly associated with facial EMG recordings. Specifically, the EMG signals will be visually inspected for non-physiological spikes, eye blinks, speech-related artifacts, or excessive movement. Trials containing artifacts (e.g., signals exceeding ±3 SD from baseline) will be excluded from further analysis. If >25% of trials from a given condition are affected, the participant will be excluded from that analysis. Finally, a baseline correction will be applied relative to a pre-stimulus window to account for tonic muscle activity.

#### 2.6.2. Experiment 2

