## 3. Discussion

This study aims to provide novel insights into the psychophysiological correlates of vaccine hesitancy (VH). Grounded in the Somatic Marker Hypothesis [25], we hypothesize that bodily and emotional responses will play a crucial role in shaping vaccination attitudes. By investigating sensorimotor mapping, affective learning processes, and psychological predictors of VH, we seek to contribute to a more comprehensive understanding of this phenomenon.

### 3.1. Experiment 1

We predict significant differences in motor evoked potentials (MEPs) between vaccine-hesitant and vaccine-accepting individuals when exposed to COVID-19 vaccination imagery. Specifically, hesitant individuals may exhibit reduced MEP amplitudes in the deltoid muscle—a key muscle involved in vaccine administration—suggesting altered sensorimotor resonance in response to vaccination stimuli. This would align with previous research on embodiment, which posits that motor responses are modulated by observed actions [48,49]. The sensorimotor resonance may serve as a proxy for embodied affective states such as disgust or fear—emotions that are central to the Somatic Marker Hypothesis, which emphasizes the role of visceral and emotional signals in guiding behavior and cognition [25]. Therefore, a decrease in MEP amplitude may indicate a disruption of somatic marker signals, given that corticospinal excitability is sensitive to modulation by negative emotional states. This interpretation is supported by prior work demonstrating the influence of emotions—particularly aversive or defensive states on motor system activity [39,40,41,50,51,52,53]. We suggest that motor resonance changes, in this context, may index the embodied affective experience central to the SMH, thereby linking motor excitability to emotional and interoceptive processing.

Additionally, we anticipate increased facial electromyography (EMG) activity in the levator labii superioris and corrugator supercilii muscles in vaccine-hesitant individuals, reflecting higher levels of disgust and fear responses. If confirmed, these results would support the hypothesis that VH is influenced by affective biases linked to disgust sensitivity and anxiety [9,21].

### 3.2. Experiment 2

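### The facial-EMG artifact example (±3 SD from baseline) cuts on the outcome itself, so it can remove genuine strong responses and shrink the hypothesised group difference

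*Protocol article*

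**What the plan says.** The Electromyography (EMG) part of section 2.6.1 sets out the facial-EMG processing in this order:

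- Visual check: "the EMG signals will be visually inspected for non-physiological spikes, eye blinks, speech-related artifacts, or excessive movement".
- Trial exclusion: "Trials containing artifacts (e.g., signals exceeding ±3 SD from baseline) will be excluded from further analysis".
- Participant exclusion: "If >25% of trials from a given condition are affected, the participant will be excluded from that analysis".
- Baseline correction: "Finally, a baseline correction will be applied relative to a pre-stimulus window to account for tonic muscle activity".

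Section 2.8.1 analyses the resulting activity in a mixed ANOVA of group by muscle by condition. Section 3.1 gives the expected direction: "we anticipate increased facial electromyography (EMG) activity in the levator labii superioris and corrugator supercilii muscles in vaccine-hesitant individuals", interpreted as "reflecting higher levels of disgust and fear responses".

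**The concern.** The quantity that triggers exclusion and the quantity being measured are the same. After baseline correction, the EMG outcome is how far muscle activity departs from the pre-stimulus level. A cutoff expressed as distance from baseline therefore treats a large enough true response as an artifact. The text has no step that separates a genuine contraction beyond the limit from a spurious one. The blinks, speech, movement and spikes that one would want removed are already covered by the visual check.

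The participant rule adds to this. It counts artifacts of every kind and applies per condition. Someone who reacts strongly to one condition could reach the limit there and, if the ANOVA uses only participants with complete cells, lose the other conditions too.

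What is at stake is sensitivity. If the hypothesis in section 3.1 is true, more trials and participants are removed from the group expected to respond more, and a null EMG result becomes hard to interpret.

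**Working it through.** The article gives no figure for the effect of this rule, so there is none to reproduce. The check asks what the rule does under stated assumptions.

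**Inputs from the article:** limit of ±3 baseline SD; participant limit of more than 25% of trials in a condition; 20 participants per group (section 2.1.1); α = 0.05 (section 2.8).

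**Assumptions:** the limit is applied to a trial-level value X ~ Normal(μ, s), in baseline-SD units. Section 2.7.1 gives 20 and 16 as MEP counts; both are assumed here to serve as facial-EMG trial counts. More than 25% then means at least 6 of 20 or at least 5 of 16.

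**Step 1: one participant, s = 1.**

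- Trials lost: p = P(|X| > 3) = 1 − Φ(3 − μ) + Φ(−3 − μ).
- Retained mean: μ + [φ(−3 − μ) − φ(3 − μ)] / [Φ(3 − μ) − Φ(−3 − μ)].
- Participant lost: P(Bin(20, p) ≥ 6) or P(Bin(16, p) ≥ 5).

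| True mean μ | Trials lost | Retained mean | Participant lost (20 trials) | Participant lost (16 trials) |
|---|---|---|---|---|
| 0 | 0.3% | 0.00 | 0.00 | 0.00 |
| 1 | 2.3% | 0.94 | 0.00 | 0.00 |
| 2 | 15.9% | 1.71 | 0.08 | 0.10 |
| 2.5 | 30.9% | 1.99 | 0.62 | 0.58 |

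For a true group difference of 1.0 SD with trial removal only:

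- means 0 vs 1 keep 0.94 − 0.00 = 0.94;
- means 1 vs 2 keep 1.71 − 0.94 = 0.77.

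**Step 2: both exclusions together.** This simulates 20 per group and 20 trials, with a between-person SD of 0.7 (assumed), 4000 runs, and a two-sided t test on participant means in a single condition.

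| Means, accepting / hesitant | Trial SD s | Participants lost, accepting / hesitant | Difference before → after | Power before → after |
|---|---|---|---|---|
| 0 / 0 | 1 | 0.2% / 0.1% | 0.01 → 0.01 | 0.05 → 0.05 |
| 0.5 / 1 | 1 | 0.6% / 3.3% | 0.49 → 0.41 | 0.55 → 0.50 |
| 1 / 2 | 1 | 3.3% / 29.1% | 0.99 → 0.59 | 0.99 → 0.86 |
| 1 / 2 | 2 | 22.7% / 60.6% | 1.01 → 0.34 | 0.96 → 0.36 |

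The third row falls below the 0.77 of step 1 because participants now vary and the strongest responders are lost altogether. This is a two-group contrast within one condition. The group-by-condition interaction of the planned ANOVA was not computed.

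**Step 3: the raw-sample reading.** If the limit applies to each sample, a trial of n independent Gaussian noise samples is flagged with probability 1 − 0.9973ⁿ. That is 24% for n = 100, 74% for n = 500 and 93% for n = 1000. Simulated Gaussian noise in the stated 100–500 Hz band, over an assumed 1-second window, gives about 98%. In most of these cases nearly every participant in both groups would breach the 25% limit.

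**The case against.** The strongest counter-argument is that the text excludes artifacts and offers ±3 SD only as an example, after listing visual inspection. Neither the signal (sample or trial value) nor the baseline is defined, and such detail may sit in a fuller document. That stands as far as it goes: the article does not say that every trial beyond ±3 SD is removed mechanically. But it does name that amplitude as a mark of an artifact, and it gives no other numeric amplitude criterion. Applied as written, it selects on the outcome.

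Several stronger readings are tempting and are not supported:

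- **That hesitant participants will be lost preferentially.** This follows only if they respond more. With equal responses, exclusion is equal and the rejection rate stays at 5%, so there is no inflation of false positives.
- **That the bias is large.** At low response levels it is small (0.49 to 0.41). The documents do not say where responses will lie.
- **That the raw-sample figures show selective loss.** They show an unworkable rule in both groups, which is a different problem.
- **That the 25% rule removes strong responders from the study.** It works per condition, counts all artifact types, and removes a person only from that analysis.
- **That inspection is unmasked.** The article is silent on masking, and silence in a condensed article is not evidence of a defect.

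The objection is also right about rank. Section 2.1.2 sizes Experiment 1 on the MEP analysis of deltoid and extensor carpi radialis, not on facial EMG.

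**Conclusion.** The point holds at moderate severity. A cutoff measured from baseline, on an outcome that is itself departure from baseline, can discard genuine strong responses. If the article's own prediction is true, the consequence is attenuation and lost power; if the groups respond alike, the rule is neutral.

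The size cannot be fixed from the document. It depends on the assumed response means, the trial-to-trial SD, the between-person SD and the trial count, and on the limit being applied to trial-level values. Across the scenarios shown, it runs from slight, when mean responses stay at or below about 1 baseline SD and the trial SD is 1, to serious, when they reach about 2 SD or more.

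**What to change.** - Remove ±3 SD from baseline as an exclusion criterion.
- Reject trials on features that do not depend on response size: contamination of the pre-stimulus window, amplifier saturation, and the blinks, speech, movement and non-physiological spikes already listed.
- Keep large responses, and limit their influence by log transformation or within-person standardisation.
- Report rejected trials and excluded participants by group and condition.
- Add a sensitivity analysis that applies the ±3 SD rule, with the signal and the baseline defined.

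The cost is a change of wording before analysis, plus one extra analysis and one table. The downside is that some noisy trials will be kept.
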